## Abstract

**Introduction:**

The number of clinical research projects on stem cell therapy for stroke has increased annually with the rapid development of stem cells and regenerative medicine technologies. Some evidence indicates that negative emotions can affect the recruitment, compliance, retention, satisfaction, and even treatment outcomes of participants in clinical research. However, knowledge is insufficient regarding patients’ negative emotions associated with their participation in potential stem cell clinical research studies. Therefore, the study aims to investigate the negative emotions and main influencing factors for potential participants in clinical research on stem cell therapy for stroke.

**Methods:**

This study protocol follows the Strengthening the Reporting of Observational Studies in Epidemiology Good Practice for Reporting Observational Studies. The questionnaire for this study will include 59 questions for potential participants regarding (1) their demographic characteristics, and (2) their levels of anxiety, depression, social support, general self-efficacy, and self-perceived burden.

**Discussion:**

This study’s main strength is that it will contribute evidence on key predictors of negative affectivity in potential participants undergoing clinical trials of stem cell therapy for stroke. The results will support stem cell clinical center researchers in intervening in potential participants’ negative emotions, which is important for clinical research managers and policymakers worldwide.

**Conclusion:**

The study protocol developed in this study was validated through a rigorous development process, demonstrating scientific validity for negative affect evaluation in stem cell clinical research. This instrument provides clinicians with a standardized assessment protocol to monitor treatment-emergent emotional distress during experimental interventions, showing particular promise in identifying early psychological risks associated with novel biological therapies.

## Introduction

1

The *Annual Report on the Progress of Clinical Trials of New Drug Registration in China (2022)* released by the Drug Evaluation Centre of the State Food and Drug Administration (1), the Drug Clinical Trial Registration and Information Disclosure Platform recorded over 3,410 clinical trials in 2022. A record number of 46 new clinical trials of cell and gene therapy products were registered in 2022. The approval rate for clinical trials was 55.8%, while the efficiency of clinical trial initiation improved, with the overall proportion of participant recruitment initiated within 6 months reaching 91.5%. As of December 2023, the registered work of 141 stem cell clinical research institutions had been completed in China, and 127 stem cell clinical research projects had been finalized. Further, the number of clinical research participants has continued to increase.

For new treatment technologies, participants may experience varying degrees of negative emotions because they are concerned about the trial’s safety and effectiveness. Peng et al. (2) found that many patients with hemophilia who participated in clinical trials showed various physical and psychological symptoms, such as anxiety and depression. Additionally, participants lack an understanding of how they perceive stimuli and their coping strategies (3).

Negative emotions can affect treatment outcomes negatively. Some studies (4–8) have shown that negative emotions increase mortality and affect patients’ treatment outcomes, functional recovery, social activities, and quality of life. Negative emotions may cause participants to experience depression, cognitive decline, inattention, or distraction (9), which subsequently leads to reduced participant compliance and negative impacts on investment and cooperation in the treatment process. Clinical studies have shown that negative emotions increase the risk of adverse reactions (10). For example, participants with depressive symptoms may experience serious adverse events in clinical studies, such as suicide and self-harm (11, 12). Hence, negative emotions influence the participation of potential participants in clinical research. Moreover, negative affect may cause participants to be less interested in participating in clinical research, thereby reducing their participation, compliance, and retention. Chuangu et al. (13) found that anxiety and depression were independent risk factors for clinical trial participants withdrawing from studies. Therefore, it is particularly important to screen and intervene in response to negative emotions among potential participants in clinical research.

However, researchers typically do not adequately assess participants’ negative emotions in the clinical research process because the purpose and focus of stem cell clinical research is to examine the effects of treatment. Therefore, it is difficult for medical staff to detect the negative emotional status of stem cell clinical research participants or to implement timely and effective intervention measures.

As the ‘bio-psycho-social-environmental’ medical model becomes mainstream, the focus of clinical research should not be limited to the therapeutic effect. The participants’ negative psychological emotions must be seriously considered. The incidence of anxiety, depression, and negative emotions is high after a stroke (14) and thus negatively impacts the therapeutic effect (6, 8).

This project examines the negative emotional characteristics of potential participants for stem cell therapy in clinical research on stem cell therapy for stroke. The results of this study will provide a basis for the psychological care of this group during their formal participation in stem cell clinical research. Therefore, this study is intended to promote the screening and improve the mental health of this patient group and ensure the smooth progression of participants in stem cell clinical research.

### Research purpose

1.1

This survey-based clinical observational study aims to use questionnaires to (1) evaluate the anxiety and depression status of participants in clinical research on stem cell therapy for stroke before receiving treatment and (2) analyze the influencing factors.

## Materials and methods

2

### Study design

2.1

This study involved a multidisciplinary collaborative research team comprising experts in neurology, nursing, psychology, statistics, stem cells, and regenerative medicine. After the team members had discussed and formulated the research plan, it was submitted to the School of Nursing expert committee at Dalian Medical University for review. The expert committee reviewed and guided the revision and improvement of the standardized selection and use of scales. The revised research plan was also submitted to the expert committee for review and approval. The technical roadmap of the study protocol is shown in Figure 1.

**Figure 1 fig1:**
[figure not shown]
Research protocol diagram.

### Participants

2.2

Potential participants will be recruited from a large general university hospital in Liaoning, China. Patients with stroke who meet the inclusion and exclusion criteria will be identified by reviewing their case information. To ensure that meaningful and accurate data are obtained, strict adherence to inclusion and exclusion criteria is required in pretrial participant selection.

#### Inclusion and exclusion criteria

2.2.1

The inclusion criteria are as follows: (1) Those diagnosed with ischemic stroke according to the standard diagnosis in the *Chinese Cerebrovascular Disease Diagnosis and Treatment Guidelines 2021* and brain computed tomography (or magnetic resonance imaging); (2) Aged ≥18 years old; (3) NIHSS score of 1 to 15 points; (4) patients with acute ischemic stroke within 72 h of onset; (5) the infarct area of the stroke is the internal carotid artery system, involving only one cerebral hemisphere; (6) the TOAST classification is large artery atherosclerosis or cardioembolism. (7) Patients with stroke who have learned about stem cell clinical research and are willing to participate in this study; (8) Patients who voluntarily accepted this study investigation and signed informed consent; (9) Patient have not previously used stem cells for stroke treatment.

The exclusion criteria are as follows: (1) Patients with congenital malformations of cerebral arteries and veins, including those with complete occlusion of the M1 segment of the middle cerebral artery or patients with severe disease such as cancer and stroke; (2) Patients with Parkinson’s disease, Alzheimer’s, and motor neuron disease; patients with Yuan disease, epilepsy and other neurological diseases; (3) Patients with schizophrenia, bipolar disorder, autism and other mental and psychological diseases; (4) Patients with immunodeficiency virus (HIV), syphilis, hepatitis B and C and with infectious diseases; (5) Patients with stroke during pregnancy and lactation; (6) Patients with stroke with communication disorders.

### Pre-test

2.3

A pre-test was used to identify potential problems and improve the questionnaire. Moreover, it helped ensure the questionnaire was readable, understandable, and logical.

#### Rigorous questionnaire design

2.3.1

Rigorous design ensures that the questionnaire is clear and that none of the included items is ambiguous or misleading. Considering the background and level of the intended respondents and using concise language and clear instructions reduces interpretation errors.

#### Survey piloting

2.3.2

The questionnaires were distributed after the research project was introduced to potential participants who had not participated in the questionnaire design of the survey. Participation in the study was voluntary. During the pre-test, we collected the participants’ feedback and suggestions on the content and other aspects of the questionnaire.

#### Data collection

2.3.3

We conducted in-person, face-to-face interviews with participants to gain an in-depth understanding of their views, experiences, and suggestions. Participants were closely observed, and relevant data was collected. Next, we analyzed their performance and reactions in the pre-test.

Participants were also asked to record their thoughts, feelings, and experiences in the pre-test to provide more detailed and in-depth feedback and ensure the survey was clear and comprehensible. To make the expressed content more comprehensive, clear, and accurate, some adjustments were made to the communication strategies to ensure a completion time of 20 min. The Daily Living Ability Scale scores were also extracted from the cases. The study group and expert committee discussed the modifications until a consensus was reached.

#### Data collection consistency

2.3.4

The investigators used a unified method to conduct the questionnaires to ensure consistency and comparability of the data.

#### Data verification

2.3.5

The data’s completeness, consistency, and accuracy were checked before analyzing them and eliminating or correcting abnormal or erroneous data. The accuracy and reliability of the questionnaire were evaluated using a test of reliability and validity. The data were collected and analyzed in a timely fashion and feedback and improvement measures were provided based on the results. This improves the questionnaire’s quality and increases the accuracy and reliability of future surveys. Implementing these quality control measures helps ensure the quality of the descriptive questionnaire and improves the reliability and accuracy of the data.

### Questionnaire

2.4

#### General information questionnaire

2.4.1

After reviewing the literature and based on discussions with expert members of the research team, we designed a general information questionnaire to collect data on the demographic and disease characteristics of patients with stroke. We also selected a scale that has been tested for reliability and validity in China to assess potential participants in clinical research on stem cell therapy for stroke, depression, self-efficacy, social support, and self-perceived burden.

The general patient information questionnaire includes questions regarding demographic factors, socioeconomic status, health status, and biochemical parameters. The response format is closed-ended and has the following structure: gender (female, male), age (≤ 44 years, 45–59 years, 60–74 years, 75–89 years, ≥ 90 years), marital status (married, single, widowed, divorced), education level (elementary school and below, junior high school, high school, university, graduate school), living status (living with family, nursing home, alone), place of residence (urban, rural), medical payment method (self-pay, resident medical insurance, Employee Medical Insurance), per capita monthly family income (CNY ≤ 1,000, CNY 1001–3,000, CNY 3001–5,000, CNY 5001–7,000, CNY > 7,000), sleep duration per night (≤ 4 h, 5–6 h, 7–8 h, ≥ 8 h). Questions will also include regarding the presence of other diseases (none, yes), the respondents’ ability to conduct activities of daily living (completely need help in life, need much help in life, need some help in life, basically capable of self-care), their fibrinogen level (normal, elevated, reduced), and their plasma D-Dimer level (normal, elevated, reduced).

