von Känel et al. (22) studied the longitudinal association between cognitive depressive symptoms and D-dimer levels in patients following acute myocardial infarction. They found that D-dimer was independently associated with depression. Patel et al. (23) found that elevated fibrinogen levels were consistently observed in patients with depression. The methodological advantage of this study is that it includes objective clinical test indicators (e.g., plasma D-dimer, fibrinogen) as independent variables, which reduced the risk of the research results being entirely caused by self-report bias. Another advantage of this study is that the assessment tool has been validated on a large scale in China, and the scale has good reliability and validity (24, 25). Epidemiological evidence shows that the incidence of stroke in young adults is on the rise worldwide (26). The incidence of stroke in adults aged 20–44 in the United States increased from 17 per 100,000 American adults in 1993 to 28 per 100,000 in 2015 (27). The incidence of stroke in young people in China is also on the rise (28). Therefore, the age standard for inclusion in this study is ≥18 years old, rather than being limited to elderly patients with stroke, which is particularly important given the trend of more strokes occurring among young people. The other advantage of this study is that the research participants are stroke patients willing to participate in stem cell clinical research, which can improve the questionnaire’s effective response and recovery rates.

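### The sleep bands overlap at 8 h and leave gaps between whole hours; separately, age, fibrinogen and D-dimer are collected only in bands, which loses information of assumption-dependent size

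*Protocol article*

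**What the plan says.** Section 2.4.1 (General information questionnaire) introduces its items with "The response format is closed-ended and has the following structure" and then lists the categories. Four of them matter here.

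- Sleep: "sleep duration per night (≤ 4 h, 5–6 h, 7–8 h, ≥ 8 h".
- Age: "age (≤ 44 years, 45–59 years, 60–74 years, 75–89 years, ≥ 90 years".
- Fibrinogen: "their fibrinogen level (normal, elevated, reduced".
- D-dimer: "their plasma D-Dimer level (normal, elevated, reduced".

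The article gives no rule for an answer of exactly 8 h or between whole hours, no laboratory cut-offs, and no statement that exact values are kept alongside the bands.

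The Discussion (section 4) counts it as a methodological advantage that "it includes objective clinical test indicators (e.g., plasma D-dimer, fibrinogen) as independent variables", and cites published associations of both markers with depression as the reason. Section 3.2.3 plans a multiple linear regression on a total score and wants to quantify how much each factor contributes to the total variation.

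**The concern.** There are two faults of different kinds.

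The first is a wording error in the sleep item. The two upper boxes share a value, so identical patients can be placed in different groups. The single-factor test and any regression coefficient for sleep then partly reflect interviewer or patient habit. Section 2.3.1 presents the questionnaire as free of ambiguous items, and this item is ambiguous on its face.

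The second is a design choice. A banded predictor explains less of the outcome than the number behind it, so its estimated contribution to the variation is too small when the true relation is roughly linear. That quantity is what section 3.2.3 sets out to measure. The loss falls most heavily on the two markers, which the Discussion promotes as the safeguard against results that rest entirely on self-report.

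**Working it through.** **The plan's own figure.** Section 2.5 uses 22 variables at 5–10 cases each: 22 × 5 = 110 and 22 × 10 = 220. Adding 10% gives 121 and 242. The chosen 230 lies inside that range. Taking the 10% back off, 230 / 1.10 = 209 usable forms, which is used for power below.

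**Sleep: overlap and gaps.** The bands are ≤ 4, 5–6, 7–8 and ≥ 8.

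- The value 8 belongs to both the third and the fourth band. This needs no assumption.
- Values strictly between 4 and 5, or between 6 and 7, belong to none. This matters only if answers are not in whole hours.

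To judge the size, assume normally distributed sleep with mean μ and SD σ. The share answering exactly 8 in whole hours is Φ((8.5 − μ)/σ) − Φ((7.5 − μ)/σ). The share answering 4.5 or 6.5 in half hours is the sum of the two corresponding half-hour intervals.

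| Assumed mean, SD (h) | Exactly 8 h (whole-hour answers) | 4.5 or 6.5 h (half-hour answers) |
|---|---|---|
| 6, 1.5 | 11% | 21% |
| 6.5, 1.5 | 16% | 19% |
| 7, 1.5 | 21% | 16% |
| 6.5, 1.2 | 16% | 21% |

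None of these means or SDs is in the protocol.

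**Banding: information kept.** For a standard normal predictor cut at c₁ < c₂ < …, band k has share pₖ = Φ(cₖ) − Φ(cₖ₋₁) and mean mₖ = (φ(cₖ₋₁) − φ(cₖ))/pₖ. The share of linear information kept is Σ pₖmₖ².

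*Age*, in the five stated bands (cuts at 44.5, 59.5, 74.5 and 89.5 years). With an assumed mean of 65 and SD of 12:

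- the band shares are 0.044, 0.280, 0.462, 0.194 and 0.021;
- the band means are −2.118, −0.953, 0.146, 1.249 and 2.410;
- the sum is 0.882, a loss of 12%.

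Over means of 60–70 and SDs of 10–14, the share kept runs from 0.840 to 0.905, a loss of 10–16%. The expected number aged 90 or over at mean 65, SD 12 is 230 × (1 − Φ((90 − 65)/12)) = 4.3. Over the same grid it runs from 0.3 to about 18.

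*Fibrinogen and D-dimer.* The shares reduced and elevated are not given, so a range is shown.

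| Reduced / elevated (assumed) | Kept | Lost |
|---|---|---|
| 5% / 40% | 0.732 | 27% |
| 2.5% / 30% | 0.664 | 34% |
| 2.5% / 20% | 0.592 | 41% |
| 1% / 10% | 0.404 | 60% |
| 2.5% / 2.5% | 0.273 | 73% |
| none / 50% | 0.637 | 36% |
| none / 20% | 0.490 | 51% |
| none / 10% | 0.342 | 66% |

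As a hand check of the row with none reduced and 20% elevated: φ(0.8416)² / (0.2 × 0.8) = 0.2800² / 0.16 = 0.490.

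The 27–73% range covers the splits shown and is not a bound. With 5% elevated and none reduced, only 0.224 is kept.

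**What this means for power (illustration).** Assume a true correlation of 0.20, n = 209 and two-sided α = 0.05 (the article gives 0.05 without sidedness). Power = Φ(atanh(0.20√k) × √206 − 1.96), where k is the share kept.

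- Exact value, k = 1: 83%.
- k = 0.88 (typical for age): 78%.
- k = 0.64: 64%.
- k = 0.50: 53%.

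**The case against.** The case for leaving this alone has several parts.

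- *Whole-hour answers.* If sleep is given in whole hours, as the integer limits suggest, the gaps disappear. That is fair, but the overlap at 8 h remains, and it occurs at a whole hour.
- *One variable among many.* The overlap touches one of 22 variables and only the boundary between two adjacent groups. This stands as a limit on its importance.
- *Reference-range categories are defensible.* If mood changes only above a threshold, normal/elevated/reduced is interpretable, and a linear-information measure overstates the loss. This stands: the loss figures hold only for a linear effect. The form as described nevertheless keeps no number with which to check the shape.
- *The article may condense the form.* Exact values may sit in the database. The article neither says so nor excludes it. Their availability is inferred: age is needed for eligibility (section 2.2.1), patients are identified from case information (2.2), a daily-living score was already extracted from the cases (2.3.3), and the markers are laboratory tests.

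Three stronger readings are tempting, and the document does not support them.

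- A reader might infer that all four variables misclassify patients. Only sleep does. The age bands are exclusive and exhaustive in completed years, and nothing shows that the laboratory categories place anyone wrongly.
- A reader might infer that up to half the information is lost throughout. That is far too high for age, and for the markers it is neither established nor an upper limit.
- A reader might infer that banding forces 11 dummy terms (age 4 + sleep 3 + fibrinogen 2 + D-dimer 2) into the model in place of 4 slopes. Section 3.2.3 enters only factors selected beforehand, no coding is stated, and ordered bands could be entered as scores. Eleven is a ceiling.

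**Conclusion.** The point holds in two parts of unequal certainty.

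The sleep item is defective as printed. The overlap at 8 h is certain from the text, nothing elsewhere in the article resolves it, and the gaps add to it if fractional hours are reported. Under the assumed sleep distributions, about 11–21% of whole-hour answers would fall on the shared value.

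Banding age, fibrinogen and D-dimer is an avoidable weakness rather than an error. The loss is modest for age. It is potentially large for the markers, the variables for which the article claims a methodological advantage. The marker figure depends on an unknown split, and all loss and power figures depend on a normal predictor and a linear effect. D-dimer is likely to be skewed (an assumption), so its figures apply on a transformed scale.

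Neither part undermines the study. Both merit correction because correction is cheap.

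**What to change.** - **Sleep.** Record usual hours as a number, or make the bands exclusive and exhaustive, for example <5, 5 to <7, 7 to 8 and >8 h. For forms already completed, merge the top two bands in the analysis, or keep them and disclose the overlap.
- **Age, fibrinogen, D-dimer.** Record age in years and the two laboratory values as measured, or recover them from the case record. Enter them as continuous terms, with D-dimer log-transformed, and keep the present bands for the descriptive table.

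The cost is small: revised wording for one item and a few numeric fields to extract. One limit should be acknowledged. Table 1 schedules data collection from 1 September 2024 to 28 February 2025, so exact sleep hours may not be recoverable for completed forms. Age and laboratory values probably are, provided the case record holds them.

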#### Additionally included scales

2.4.2

We will include the Generalized Anxiety Disorder 7-item scale (GAD-7) to assess the potential participants’ anxiety symptoms in the past 2 weeks. Each item ranges from 0 (never) to 3 (almost every day), with a total score of 0–21; higher scores indicate more severe anxiety symptoms (15).

The Patient Health Questionnaire (PHQ-9) comprises nine items to assess potential participants’ feelings and depressive symptoms in the past 2 weeks. Each item is scored from 0 (never) to 3 (almost every day), with the total score ranging from 0 to 27. Higher scores reflect a more serious degree of depressive symptoms (16).

The Chinese version of the General Self-Efficacy Scale (GSES-C), which has high acceptance and good reliability, is used to assess potential self-efficacy. The scale contains 10 items, and each item has four options: 1 = completely incorrect, 2 = moderately correct, 3 = mostly correct, and 4 = completely correct. Higher scores indicate better self-esteem. In addition, the scale has been shown to have high efficiency (17).

The Social Support Rate Scale (used) evaluates the social support of potential participants. The total scale score is the sum of the scores of the 10 items. The total scale score ranges from 12 to 66 points. A low level of social support is ≤22 points. The medium level ranges from 23 to 44 points, and the high level 45–66 points. The higher the total score, the higher the social support (18).

The Self-Perceived Burden Scale (SPBS) assesses the burden experienced by potential participants. The scale has 10 items. The sum of the scores for each item is the total SPBS score. The higher the score, the heavier the burden. This scale has been used to evaluate patients with stroke in China and has high acceptance and reliability (19).

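### Sleep duration is a candidate factor for a PHQ-9 total that, with standard item content, itself contains a sleep item, so part of any association is built in

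*Protocol article*

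**What the plan says.** Section 2.4.2 describes the depression measure: "The Patient Health Questionnaire (PHQ-9) comprises nine items to assess potential participants’ feelings and depressive symptoms in the past 2 weeks". The scoring follows: "Each item is scored from 0 (never) to 3 (almost every day), with the total score ranging from 0 to 27". No sub-score and no score with items left out is mentioned, and no other depression scale is listed.

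Section 2.4.1 lists the general factors, among them "sleep duration per night (≤ 4 h, 5–6 h, 7–8 h, ≥ 8 h"), a four-category variable.

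Section 3.2.1 tests the general factors against the scale scores by t-test or analysis of variance, or by non-parametric tests if the assumptions fail. Section 3.2.3 carries the significant factors into a multiple linear regression and aims to quantify each factor's share of the variation. Its outcome is a total score of negative emotions, which the article does not define further.

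**The concern.** The article does not reproduce the PHQ-9 items. On the assumption that the standard instrument is used unmodified, one item asks about trouble with sleep. A patient who sleeps four hours or less is likely to score on that item, and that score is part of the total. Comparing PHQ-9 totals across sleep categories is therefore partly a comparison of sleep with itself. Some association would be expected even if sleep duration had nothing to do with the other eight symptoms.

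The planned sequence passes this on. A factor that is significant in the single-factor test enters the regression and is credited with a share of explained variation. The article wants the results to guide targeted psychological care and the use of nursing resources (section 4). Sleep duration could be named an influencing factor of depression when the data show little more than that short sleepers report sleep trouble.

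**Working it through.** **1. The plan's own figures.**
- PHQ-9 range: 9 items × 3 = 27. This reproduces.
- Questionnaire length: the abstract states "The questionnaire for this study will include 59 questions for potential participants". The count is 13 general items + 7 (GAD-7) + 9 (PHQ-9) + 10 (self-efficacy) + 10 (social support) + 10 (self-perceived burden) = 59. No second depression scale is hidden in the count.
- Sample size (section 2.5): 22 × 5 = 110 and 22 × 10 = 220; × 1.10 gives 121 and 242. The target is 230, used below.

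**2. Correlation induced by the overlap.** Suppose sleep duration correlates ρ (absolute value) with the sleep item and zero with the other eight items. Then

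induced r = ρ × SD(item) / SD(total).

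With nine items of equal variance and common inter-item correlation c, SD(total) = SD(item) × √(9 + 72c), so induced r = ρ / √(9 + 72c).

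Neither ρ nor c is in the article. The assumed ranges are ρ = 0.3 to 0.7 and c = 0.2 to 0.5.

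| c | √(9 + 72c) | ρ = 0.3 | ρ = 0.7 |
|---|---|---|---|
| 0.2 | 4.84 | 0.062 | 0.145 |
| 0.5 | 6.71 | 0.045 | 0.104 |

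The range is about 0.05 to 0.15. A central case with ρ = 0.6, item SD 1.0 and total SD 5 gives 0.6 × 1.0 / 5 = 0.12. It implies c = (25 − 9)/72 = 0.22.

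**3. How often sleep is flagged at two-sided 0.05, N = 230.** Sleep duration has four categories, so the natural test in section 3.2.1 is an F test on 3 and 226 degrees of freedom (critical value 2.645). Its non-centrality is λ = N r² / (1 − r²), taking r as the between-group effect. For a one-degree-of-freedom correlation test, the Fisher-z shift is atanh(r) × √227.

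| Induced r | λ | Four-group ANOVA | Fisher-z shift | 1-df correlation test |
|---|---|---|---|---|
| 0.05 | 0.58 | 9% | 0.75 | 12% |
| 0.12 | 3.36 | 30% | 1.82 | 44% |
| 0.15 | 5.29 | 46% | 2.28 | 62% |

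If only 230 × 0.9 = 207 questionnaires are usable, the central ANOVA figure is about 27%.

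**4. If the regression outcome is the GAD-7 and PHQ-9 sum.** The range becomes 21 + 27 = 48, and the sleep item falls from 3/27 = 11% of the points to 3/48 = 6%. With 16 items of equal variance and c = 0.22, SD(total) = √(16 + 240 × 0.222) = 8.33 item SDs. The central induced r is 0.6 / 8.33 = 0.072, and λ = 230 × 0.072² / (1 − 0.072²) = 1.20, which gives about 13% for a four-group comparison.

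**5. Reliability after removing items.** Alpha = k c / (1 + (k − 1)c) with c = 0.22:
- nine items: 0.72
- eight items, without sleep: 0.70
- four items, without sleep, fatigue, appetite, concentration and slowing: 0.53

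Under the assumption in step 2, removing the sleep item takes the induced correlation to zero and the flag rate back to 5%.

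**The case against.** The strongest objection is that nothing in the quoted scoring is wrong. The PHQ-9 total is a standard score, the article does not give the item content, and an item-level sensitivity analysis often sits in an analysis plan that is not shown. The first part is true, and the item content has to remain a stated assumption. But the article itself fixes both the score and the factor, and describes how they are tested against each other. The overlap follows from those stated choices.

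A second objection is that the size is constructed: sleep duration is tied to one item and exactly unrelated to eight. That is fair. The calculation isolates what overlap alone would do and does not predict the observed association. It also has to respect the four categories, which is why 30% and not 44% is the central figure. Inputs chosen at their extremes (ρ = 0.7, item SD 1.1, total SD 4) would give r = 0.19 and, by correlation test, 84%. With equal items they imply an alpha of about 0.36, which is implausible for a scale that the article describes as reliable.

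Three stronger readings are tempting and are not supported.
- A reader might infer that the regression outcome is the PHQ-9 total. Section 3.2.3 does not say so.
- A reader might infer that the acute stroke inflates the other physical items, since entry is limited to "patients with acute ischemic stroke within 72 h of onset". The PHQ-9 looks back two weeks. For a patient surveyed at entry, stroke symptoms cover at most about 3 of 14 days. The article also collects daily-living ability in four grades (section 2.4.1), which may absorb part of such an effect. Nothing in the article allows this part to be sized.
- A reader might infer a mismatch with the rationale for D-dimer, because the cited work "studied the longitudinal association between cognitive depressive symptoms and D-dimer levels in patients following acute myocardial infarction". The next sentence of section 4 summarises the finding as an association with depression, and fibrinogen is justified by depression in general. There is no contradiction.

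**Conclusion.** The point holds for the sleep item only. Given standard PHQ-9 content, the single-factor test of sleep duration against the PHQ-9 total has a built-in association, and so does any regression whose outcome includes that total. Under the assumed inputs the chance of flagging sleep from overlap alone is roughly 9% to 46% with a four-group analysis of variance at 230 patients, or about 12% to 62% with a one-degree-of-freedom correlation test, against a nominal 5%. A summed outcome lowers the figure but leaves it above 5%.

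The conclusion rests on the unmodified item content, on the assumed correlation between sleep duration and the sleep item, and on sleep being unrelated to the remaining items. It does not show that a sleep finding would be false, only that the planned test could not tell a real one from the overlap. It gives no ground for abandoning the PHQ-9 total.

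**What to change.** Keep the PHQ-9 total for description and as the main depression score. For sleep duration alone, state that both the single-factor test and the regression result will be taken from the score with the PHQ-9 sleep item omitted. If the regression outcome is a sum with the GAD-7, omit the same item from the sum. Report sleep duration as an influencing factor only if the association holds on that score.

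All nine items are already collected, so the change is a sentence or two of analysis wording plus one re-scored variable. The price is a score one item shorter for that one factor, with alpha of about 0.70 instead of 0.72 under the inputs above.

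A cognitive-affective sub-score may be reported as a sensitivity analysis. It should not be a condition that every factor must meet: with four items its alpha would be about 0.53 on the same inputs, and real associations could be discarded.
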